**3.1.5 Elimination criteria**

- Participants who are subsequently found to not fulfill the inclusion criteria after the commencement of the study will be excluded.
- Subjects who decline to participate in the prescribed examination and assessment protocol during the study will be withdrawn.
- Participants demonstrating suboptimal adherence, with cumulative exercise time falling below 80% of the prescribed amount, or those who consume medication that influences muscle or bone metabolism during the study period, will be considered non-compliant and thus removed from the trial.

1. **Sample size**

The prevalence of functional falls and fractures is a significant clinical concern and a severe consequence for patients with sarcopenia, stemming from the progressive loss of muscle mass and function. The Simple Physical Performance Measurement Scale (SPPB) serves as a pivotal efficacy indicator in this context. Drawing from extant literature ^[14]^, a 24-week exercise intervention in elderly patients with a heightened risk of falls yielded an SPPB score of 9.83 ± 1.85 in the experimental group, compared to 8.39 ± 2.52 in the control group. Employing a two-sided test with an alpha level (α) of 0.05 and a power (test efficacy) of 0.9, the calculated sample size for a single group is n = 35.6, which approximates to 36 participants. Consequently, the combined sample size for both groups amounts to 72 individuals. Factoring in a dropout rate of 20%, the total sample size required for this study is 90 cases, equating to 45 participants per group.

1. **Participant**

The proposed study aims to enroll 90 elderly patients with sarcopenia who visited the Hospital of Chengdu University of Traditional Chinese Medicine between July 2022 to August 2023. The process for inclusion involves a meticulous screening of candidates at the outpatient clinic. Potential participants are to be thoroughly informed about the study’s objectives, procedures, and potential risks. Following this educational dialogue, those who meet the study criteria and express a willingness to participate will be asked to provide informed consent and sign the corresponding consent form.

1. **Randomization and Blinding**

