**10.1 Power calculation**

The prevalence of falls and fractures due to the diminution of muscular mass and function underscores the clinical urgency and grave repercussions associated with sarcopenia. Drawing upon empirical evidence from a preceding trial targeting older adults predisposed to falls ^[14]^, the Short Physical Performance Battery (SPPB) is employed as the primary efficacy index. Utilizing a two-sided test with a power of 90% and a significance level of 5%, the requisite sample size for a single intervention group is deduced to be approximately 36. Accounting for an anticipated dropout rate of 20%, each group necessitates 45 participants diagnosed with sarcopenia.

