**10.2 Data analyses**

Following an intention-to-treat (ITT) protocol, those whose cumulative time of exercise reaches 80% of the amount to be completed and not higher than 120% of that will be classified into per protocol set (PPS). Categorical variables will be presented as percentages or frequencies. As for continuous variables, normally distributed data will be described by mean ± standard deviation, while non-normally distributed data will be described using median [interquartile range (IQR)]. Baseline demographic descriptors and outcome measures wil be compared across groups by using analysis of variance for continuous variables and the $\chi$*^2^* (or Fisher exact) test for categorical variables. Within the scope of this investigation, the Generalized Estimating Equations (GEE) framework was employed to evaluate the impact of Baduanjin exercise on sarcopenia among the elderly cohort. GEE is a robust statistical approach designed to analyze correlated data or repeated measurements over time, rendering it particularly adept at accommodating incomplete datasets and multiple observational instances.Initially, an exhaustive data cleansing and encoding procedure will be undertaken to ascertain the precision and integrity of the dataset. Continuous variables will undergo a distributional analysis to discern the necessity of transformation to align with the normal distribution assumption. Categorical variables will be delineated through frequencies and percentages.The GEE model will incorporate temporal factors as a repeated measures variable, alongside other pertinent covariates that may influence the outcomes, such as age, gender, and baseline muscle mass index. The inclusion of interaction terms pertinent to time will facilitate an in-depth assessment of the longitudinal effects of Baduanjin exercise on sarcopenia. The model’s fit will be gauged using the Quasi-likelihood under the Independence model Criterion (QIC), with preference given to the model demonstrating the minimal QIC value. Additionally, a thorough examination of model residuals will be conducted to validate the adherence to underlying assumptions.Two-sided P values of less than 0.05 will be considered statistically significant. Analyses will be conducted using SPSS version 23.0 (IBM Corp) or GraphPad Prism version 7.0 (GraphPad Software).

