**Table 2. Schedule of trial procedures**

| **Period** | **Screening** | **Intervention period** | | |
| --- | --- | --- | --- | --- |
| **Time point** | **0 wk** | **0 wk** | **12 wk** | **24 wk** |
| **Enrollment** | **×** |  |  |  |
| Eligibility screening | **×** |  |  |  |
| Informed consent |  | **×** |  |  |
| **Allocation** |  |  |  |  |
| **Intervention** |  |  |  |  |
| Non-sarcopenia control |  | **×** |  |  |
| Baduanjin exercise |  | **×** | **×** | **×** |
| Resistance training |  | **×** | **×** | **×** |
| **Assessments** |  |  |  |  |
| Physical function |  | **×** | **×** | **×** |
| Body composition |  | **×** | **×** | **×** |
| Handgrip strength |  | **×** | **×** | **×** |
| 6 m walking test |  | **×** | **×** | **×** |
| Cognitive function |  | **×** | **×** | **×** |
| Incidence of falls |  | **×** |  | **×** |

1. **References**
2. Morley JE. Sarcopenia:diagnosis and treatment[J]. *J Nutr Health Aging,* 2008, 12: 452-456.
5. Cao Li MD, JE. Morley MB. Sacropenia is recognized as an independent Condition by an International Classification of Disease, Tenth Revision, Clinical Modification(ICD-10) Code[J]. 2016, (17): 675-677.
6. Murton AJ. Muscle protein turnover in the elderly and its potential contribution to the development of sarcopenia[J]. *Proc Nutr Soc*, 2015:74(4): 387-396.
7. Yuwei Lin, Guiyu Qian, Meizhi Xu. Causes and effects of sarcopenia in the elderly[J].*Tertiary sports*, 2010.10, (110): 85-91.

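### The planned GEE does not name baseline SPPB as a covariate or say how week-0 SPPB enters; conditioning on it is a free improvement

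*Combined protocol and SAP*

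**What the plan says.** Section 10.1 states that "the Short Physical Performance Battery (SPPB) is employed as the primary efficacy index". In Table 2 the row "Physical function" is marked at weeks 0, 12 and 24, so each participant should have a baseline SPPB.

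Section 10.2 plans a GEE with time as the repeated-measures factor and unspecified interactions with time, "alongside other pertinent covariates that may influence the outcomes, such as age, gender, and baseline muscle mass index". Among candidate models, the one with the smallest QIC is preferred. The section does not mention baseline SPPB, does not say whether week 0 is one of the repeated responses, and does not identify the coefficient or visit that carries the primary comparison.

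The sample size (section 4) takes its SPPB inputs from a cited trial: mean 9.83 with SD 1.85 under the experimental exercise, and mean 8.39 with SD 2.52 under control. For 90% power at the two-sided 5% level, the section reports that "the calculated sample size for a single group is n = 35.6, which approximates to 36 participants". Allowing for 20% dropout, this becomes 45 per group. No allowance is made for covariate adjustment. Section 6 describes 1:1 allocation and no stratification by SPPB.

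**The concern.** The plan proposes to adjust for the baseline of a different variable, muscle mass index, but does not mention the baseline of its own primary outcome. An outcome's own baseline is usually a useful predictor of its later value, and using it costs nothing once it has been measured. With about 36 to 45 participants per arm and no stratification on SPPB, a chance difference in baseline SPPB is also possible, and conditioning is the efficient way to deal with it.

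What is at stake is precision and pre-specification, not validity. The text allows models of different efficiency. Because the covariate list is open and QIC guides the choice, that decision could be made after outcome data are seen.

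**Working it through.** **Inputs.** From section 4: means 9.83 and 8.39, so the difference is 1.44; SDs 1.85 and 2.52; two-sided 5%; 36 evaluable per group (45 before dropout). Pooled SD = √[(1.85² + 2.52²)/2] = √4.886 = 2.21. Assumed, because the documents give no figure: the correlation r between baseline and week-24 SPPB (0.3 to 0.7), and the ratio k of baseline SD to follow-up SD (1, 0.8, 0.6).

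**The plan's own figure.** n per group = 2(1.960 + 1.282)² × SD² / 1.44².
- With the pooled SD: 49.5, so 50 per group (50.5 by the t distribution), not 36.
- With 1.85 for both arms: 34.7, or 35.67 by the t distribution, close to the stated 35.6.
- The dropout step reproduces: 36/0.8 = 45.

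The stated size is therefore approached only if the control SD is not used. That is a separate sample-size matter. It enters here only because it sets the power from which the gain is measured: with both SDs, noncentral-t power is 77.8% at 36 per group and 86.3% at 45.

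**Variance of the week-24 contrast, relative to comparing raw week-24 scores.**
- Week 0 not modelled: 1.
- Week 0 as a response, arm means free, group-by-time contrast: 1 + k² − 2kr, which is 2(1 − r) when k = 1.
- Conditioning on baseline: 1 − r².

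The excess over conditioning is r² in the first case and (k − r)² in the second. Neither can be negative, so the direction does not depend on the assumed values; only the size does. Equality needs r = 0 in the first case or r = k in the second.

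**Power at 36 per group** (noncentral t, SD = 2.21 × √factor):

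| assumed r | week 0 not modelled | change contrast, k = 1 | baseline-adjusted |
|---|---|---|---|
| 0.3 | 78% | 63% | 82% |
| 0.4 | 78% | 70% | 84% |
| 0.5 | 78% | 78% | 88% |
| 0.6 | 78% | 86% | 93% |
| 0.7 | 78% | 94% | 97% |

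A simulation with normal data, which also counts the degree of freedom spent on the covariate, agrees: at r = 0.3, 0.5 and 0.7 it gives 64%, 78% and 94% for change and 81%, 88% and 96% for adjustment.

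**Smaller baseline SD, same n:**

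| assumed r | change, k = 0.8 | change, k = 0.6 | baseline-adjusted |
|---|---|---|---|
| 0.4 | 78% | 83% | 84% |
| 0.5 | 84% | 88% | 88% |
| 0.6 | 91% | 93% | 93% |

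Here the gap between change and adjustment is about 0 to 7 points, against about 6 to 14 points at k = 1 over the same r.

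**Correlation needed for 90% power by adjustment** (normal approximation): √(1 − 36/49.52) = 0.52 at 36 per group; √(1 − 45/49.52) = 0.30 at 45 per group.

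**The case against.** - **The list is open.** The three covariates are given as examples. A reader might infer that the plan adjusts for them and excludes baseline SPPB; the text does not say so. This stands, and the point is limited to what 10.2 leaves unnamed.
- **Week 0 may already be in the model.** With time as the repeated factor and assessments at weeks 0, 12 and 24, baseline SPPB may be a response. A group-by-time term then uses it, and both analyses are valid. This stands too: on that reading the issue is a less efficient use of baseline, not its absence.
- **The change-score penalty depends on k.** Section 3.1.3 excludes SPPB above 9 on a 0 to 12 scale, while the assumed follow-up mean in the experimental arm is 9.83. Baseline scores may therefore vary less than follow-up scores, and the penalty then shrinks as shown above. Restricting the baseline range also tends to lower r, which reduces the gain from adjustment over ignoring week 0.
- **The comparison base is pessimistic.** The gains are measured against raw scores, but three covariates are already named, so the increment from baseline SPPB may be smaller. Thirty-six is the completer count; with 45 contributing, unadjusted power is 86%.

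None of this makes either reading more efficient than conditioning on baseline. It limits how much can be claimed for the change.

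**Conclusion.** The point holds as a free improvement. Section 10.2 does not name baseline SPPB and does not say how week-0 SPPB enters. Both readings examined are at best equal to conditioning on it in large samples. In small samples conditioning costs one degree of freedom, which is negligible here unless r is near zero.

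At 36 per group, the gain over ignoring week 0 runs from about 4 points (r = 0.3) to about 19 (r = 0.7). The gain over a change contrast runs from about 18 points down to about 3 over the same range at k = 1, and is about 0 to 7 points at k = 0.6 to 0.8 with r of 0.4 to 0.6. These figures treat SPPB as approximately normal and rest on assumed r and k.

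Two stronger conclusions might be inferred and are not supported. One is that adjustment would recover most of the gap to the stated 90%: at r = 0.3 it recovers about 4 of 12 points, and at 36 per group it reaches 90% only from about r = 0.52. The other is that baseline SPPB is the strongest predictor available: that is plausible, but the documents contain no figure for it.

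**What to change.** Add to section 10.2:

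*The primary GEE has SPPB at weeks 12 and 24 as the outcome, with group, visit, group×visit, baseline SPPB, age, gender and baseline muscle mass index as prespecified covariates that are not selected by QIC; the primary contrast is the group difference at week 24.*

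Use the same form for each continuous secondary outcome, with its own baseline value. This keeps all three covariates that the plan already names. The cost is one sentence, with no new data, visits or participants. It does not replace reconciling the sample size with the two SDs quoted in section 4.

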**7.1 The Baduanjin Group**

In conjunction with health education initiatives, the Baduanjin training is conducted at a designated time and location. Each session is facilitated by an instructor with a minimum of five years’ experience in teaching Baduanjin. The training adheres to the Baduanjin standards promulgated by the State General Administration of Sports in 2006 ^[15]^. The sequence comprises a preparatory stance followed by a series of ten movements:

- Preparatory Posture
- Holding Up The Sky With Both Hands To Regulate The Sanjiao
- Draw The Bow On Both Sides As If To Shoot A Vulture
- Stretch Arms Asymmetrically To Enhance Spleen And Stomach Function
- Look Back To Treat Five Strains And Seven Impairments
- Sway The Head And Buttocks To Subdue The Heat Fire
- Touch Feet To Strngthen Kidneys And Waist
- Rise Up On Toes And Land On Heels Repeatedly To Cure Disease
- Clench The Fist And Open Eyes Wide To Enhance Vitality
- Closing Posture

The regimen is scheduled three times weekly, with each session lasting 60 minutes. This includes 15 minutes for warm-up activities, 30 minutes dedicated to the Ba Duan Jin exercises, and 15 minutes for cool-down activities, spanning a total duration of 24 weeks.

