**7.2 The Resistance training Group**

The educational component of the study on sarcopenia in the elderly is structured to provide sessions once every four weeks, each lasting no less than 30 minutes. These sessions are designed to impart knowledge on the risk factors, adverse consequences, and preventive measures associated with sarcopenia. An example of such preventive measures includes adherence to the dietary guidelines for the elderly, as revised in 2016 by the Chinese Nutrition Society, which emphasizes rational nutrition, balanced diets, and the cultivation of healthy living and eating habits. In terms of physical intervention, the study incorporates a resistance training program tailored to the geographic location of each sub-centre. The regimen consists of 60-minute sessions conducted three times a week over a 24-week period. Each training session is segmented into a 15-minute warm-up, followed by 30 minutes of resistance exercises—including Wall squat, Wall push-up, Forward lunge, Reverse triceps push-up, and Wall-supported calf raise—and concludes with 15 minutes of cool-down activities.

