**8.1 Demographics**

For the comprehensive assessment of participants in your study on sarcopenia, the following data should be meticulously collected:

- Demographic Data: This includes the participant’s name, gender, date of birth, education level, weight, height (or BMI), ethnicity, occupation, and contact address.
- General Physical Examination: Vital signs such as heart rate, pulse, respiration, and blood pressure should be systematically recorded.
- Medical and Social History:
- Current Medical History: Document any present health conditions.
- Co-morbidities and Medications: List any concurrent illnesses and current medications.
- Allergies: Note any known allergies.
- Family History: Include any relevant hereditary health issues.
- Smoking and Alcohol History: Record past and present tobacco and alcohol use.
- Additional Relevant Information: Gather details on any falls within the past year, hand dexterity (sharp hands), sleeping habits, hobbies, personality traits, social activities, and other lifestyle factors that may influence the condition.

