**8.3 Secondary outcomes**

The methodology for assessing the efficacy of the intervention on elderly patients with sarcopenia is comprehensive and multi-faceted, involving the following measures:

- Body Composition Analysis: Utilizing the DBA-510 Body Composition Analyzer, participants' body weight, body water, fat mass, fat percentage, lean body weight, BMI, and segmental muscle mass of the trunk, upper, and lower limbs will be evaluated through bioelectrical impedance analysis.
- Handgrip Strength Measurement: The JAMAR electronic grip strength meter will be employed to gauge upper limb muscle strength. Participants will perform the test standing, with arms at their sides, elbows bent at 90°, and forearms supinated, exerting maximum grip strength. The highest value from four measurements (two per side) will be recorded.
- 6-Meter Walk Test: This test assesses muscle performance by having participants walk 6 meters at their usual pace. The walking speed is calculated based on the time taken to complete the distance. The test is conducted twice, and the average time and speed are noted.
- Cognitive Function Assessment: The 30-item Montreal Cognitive Assessment (MoCA, Changsha version) will be used to measure global cognitive function. This instrument is tailored for Chinese populations and scores cognitive function across multiple domains on a scale from 0 to 30, with higher scores indicating better cognitive function.
- Incidence of Falls Tracking: Participants will maintain a "fall calendar" diary to document any falls and related medical consultations monthly. This includes accidental landings on the floor or ground or collisions with objects. The collection of fall data commences with the first intervention class and continues until the intervention's conclusion or until a participant's withdrawal, death, or loss to follow-up.

1. **Quality control**

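### Falls in the past year, the only pre-treatment fall information, could be named as a baseline covariate for the falls outcome, and the week-0 falls mark in Table 2 should be defined

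*Combined protocol and SAP*

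**What the plan says.** Section 8.1 lists fall history among the background items: "Gather details on any falls within the past year". Section 8.3 makes falls a secondary outcome, recorded in a diary kept by the participant "to document any falls and related medical consultations monthly". It fixes the start of recording: "The collection of fall data commences with the first intervention class". Recording ends with the intervention, or sooner if the participant withdraws, dies or is lost. The trial's own fall data are therefore all post-baseline, and the past-year item is the only fall information from before treatment.

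Section 10.2 describes one general GEE analysis. On time it says: "The GEE model will incorporate temporal factors as a repeated measures variable". On adjustment it names "other pertinent covariates that may influence the outcomes, such as age, gender, and baseline muscle mass index". It does not mention falls, gives no link function or follow-up offset for a count outcome, and prefers the model with the lowest QIC.

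Table 2 has a row "Incidence of falls" marked at week 0 of the intervention period and at week 24, but not at week 12. It does not say what the week-0 mark stands for.

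**The concern.** Previous falls are a natural baseline predictor of later falls, and the plan already collects them. With 90 participants followed for 24 weeks there will be few falls. Allocation under section 6 is 1:1, with no stratification by fall history described, so a chance difference between arms in the share of previous fallers is not limited by design. Because the covariate list is open and models are compared by QIC, whether to adjust for fall history could be decided after the outcome data have been seen. The undefined week-0 mark adds a smaller uncertainty about what counts as the falls response.

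At stake are some precision and some protection from chance imbalance in one secondary outcome. Sections 4 and 10.1 use falls and fractures to explain why the condition matters, so the falls result is likely to be read with interest.

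**Working it through.** The plan states no fall rate, fall count or power for falls, so there is no figure of its own to reproduce.

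**Inputs from the documents**
- 45 participants per arm (section 4).
- On-study window of 24 weeks in both arms: "spanning a total duration of 24 weeks" (section 7.1) and "conducted three times a week over a 24-week period" (section 7.2).

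**Assumed inputs (not in the documents)**
- 35% of participants are previous fallers.
- They fall k = 2 to 3 times as often as the others.
- The overall rate is 0.6 to 1.0 falls per person-year.
- Follow-up is complete.

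**1. Likely size of a chance imbalance.** The SD of the between-arm difference in the share of previous fallers is sqrt(2 × 0.35 × 0.65 / 45) = 0.101, or 10 percentage points. A 20-point difference is about 2 SD, so about 1 trial in 20 counting both directions.

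**2. Effect of a 20-point imbalance (45% v 25%) with no treatment effect.** Rate ratio = (1 + 0.45(k − 1)) / (1 + 0.25(k − 1)).
- k = 2: 1.45 / 1.25 = 1.16
- k = 2.5: 1.675 / 1.375 = 1.22
- k = 3: 1.90 / 1.50 = 1.27

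**3. Comparison with the standard error.** Each arm contributes 45 × 24/52 = 20.8 person-years, hence 12.5 falls at 0.6 per person-year and 20.8 falls at 1.0. The Poisson SE of the log rate ratio is sqrt(2/12.5) = 0.40 or sqrt(2/20.8) = 0.31. The log rate ratios from step 2 run from 0.15 to 0.24, so the shift lies between 0.15/0.40 = 0.4 and 0.24/0.31 = 0.8 of one SE. Overdispersion widens the SE and makes the shift relatively smaller.

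**4. Precision gained by adjustment.** For Poisson counts, the unadjusted variance of the log rate ratio is proportional to 1/μ + C. Here μ is the expected falls per person over 24 weeks, and C = 0.35 × 0.65 × (k − 1)² / (1 + 0.35(k − 1))² is the part due to fall history.
- C = 0.2275/1.8225 = 0.125 at k = 2, and 0.91/2.89 = 0.315 at k = 3.
- 1/μ = 1/(0.6 × 24/52) = 3.61 at the lower rate, and 1/(1.0 × 24/52) = 2.17 at the higher.
- Share of variance removed, C/(1/μ + C): from 0.125/3.74 = 3% (lower rate, k = 2) to 0.315/2.48 = 13% (higher rate, k = 3).

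This is a large-sample approximation and somewhat generous. Overdispersion, and estimating the coefficient from 90 people, take part of the gain away. Simulation over the same assumed range gives about 2-10%. A 10% lower variance shortens a confidence interval by 1 − sqrt(0.90) = 5%.

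**The case against.** **The plan does not exclude fall history, and omitting it does not bias a randomised comparison.** Both statements are correct. The covariate list is illustrative, and section 10.2 compares baseline descriptors between arms, so an imbalance would probably be noticed. Chance imbalance is already allowed for in the standard error, and step 3 shows that even a 1-in-20 imbalance would rarely pass for a treatment effect. What remains is that pre-specifying the covariate gives a small gain in precision and removes a choice that could otherwise be made after seeing the data.

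**The outcome window is already post-baseline.** This also stands. Section 8.3 starts recording at the first class, and marks at weeks 0 and 24 fit the opening and closing of a diary. The fault in Table 2 is only that the mark is not explained.

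**A stronger reading to avoid.** A reader might infer from the week-0 mark and the repeated-measures model that the 12-month recall will serve as the week-0 response. At a constant fall rate and with no offset, counts would then appear to drop by 1 − 24/52 = 54%. The documents do not support this inference. Nowhere do they place the recall in that cell, and section 10.2 does not say that falls enter the repeated-measures model. If it were done, the two arms would share the same windows, so the artefact would sit in the within-arm change and cancel from the between-arm ratio. Only on an additive scale would a baseline imbalance leak through: with 0.6 v 0.4 past-year falls per person, the difference in change would be 0.2 × (24/52 − 1) = −0.11.

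**Conclusion.** The point holds as an optional, low-severity improvement to a secondary outcome. Fall history is collected, is the only pre-treatment fall information, and is not named for the falls analysis. The expected benefit is about 2-10% lower variance of the log rate ratio, plus correction for chance imbalance in previous fallers that could by itself produce a rate ratio of 1.16 to 1.27 in about 1 trial in 20. Both figures rest on the assumed share of previous fallers, relative risk and fall rate; the documents supply none of them. The primary SPPB analysis is not affected, and the documents give no ground for saying that the planned falls comparison between arms is biased.

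**What to change.** In section 10.2, add a statement that falls from the first class to the end of each participant's follow-up will be compared between arms as a rate. Specify a log link, observed follow-up time as an offset, and a model or variance estimate that allows for overdispersion. Name falls in the past year as a pre-specified baseline covariate, and state that there is no week-0 falls response. The offset is needed because section 8.3 lets recording stop early and section 4 expects 20% dropout.

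In Table 2, relabel the week-0 falls mark as fall history / diary start.

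The cost is a short addition to the SAP and one table label, with no new data collection. Coding fall history as yes/no uses one degree of freedom; coding it as 0, 1, 2+ uses two. With few falls expected, the yes/no form is the more economical choice. The coding should be fixed before outcome data are examined.

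### Section 10.2 names no primary visit or coefficient for SPPB and does not limit the smallest-QIC rule to the working correlation, so the primary result can depend on which model the data favour

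*Combined protocol and SAP*

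**What the plan says.** Section 10.1 states that "the Short Physical Performance Battery (SPPB) is employed as the primary efficacy index", without naming a visit. Section 8.2 defines the 0 to 12 score, also without a visit. The Sample size section takes its planning values from "a 24-week exercise intervention in elderly patients with a heightened risk of falls", and Table 2 schedules physical function at weeks 0, 12 and 24.

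Section 10.2 then describes a GEE with time as the repeated factor. Age, gender and baseline muscle mass index are given as examples of covariates, so the list is open and baseline SPPB is not on it. On interactions it says: "The inclusion of interaction terms pertinent to time will facilitate an in-depth assessment of the longitudinal effects". On model choice it gauges fit by QIC, "with preference given to the model demonstrating the minimal QIC value". On scale: "Continuous variables will undergo a distributional analysis to discern the necessity of transformation to align with the normal distribution assumption". Any two-sided p below 0.05 counts as significant, and there is no multiplicity rule.

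The section does not state:
- which coefficient or contrast is the primary test;
- which models compete on QIC;
- the working correlation;
- whether week-0 SPPB is an outcome row or a covariate.

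**The concern.** Sample size and analysis should answer the same question. The first is built on the SPPB difference after 24 weeks; the second never singles that difference out. QIC rewards fit and parsimony. It does not know which coefficient carries the treatment question. If it may choose the mean model, it can remove the group-by-time terms that hold the week-24 effect, or keep them and leave two follow-up contrasts open. Two analysts who both follow section 10.2 could then report different primary results from the same data, and the stated 5% level would not describe the procedure as a whole.

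**Working it through.** **Inputs from the documents.** "yielded an SPPB score of 9.83 ± 1.85 in the experimental group", "compared to 8.39 ± 2.52 in the control group": difference 9.83 − 8.39 = 1.44; root-mean-square SD √[(1.85² + 2.52²)/2] = 2.21. Two-sided α 0.05, power 0.90, 36 per group before dropout. SPPB at weeks 0, 12 and 24.

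**Assumptions, not in the documents.** Exchangeable correlation ρ between visits of 0.3, 0.5 or 0.7. Week-12 effect 50% or 100% of the week-24 effect. The week-0 effect is zero by randomization.

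**The plan's own figure.** n per group = 2(1.960 + 1.282)² SD²/1.44².
- SD 2.21 gives 49.5.
- SD 1.85 in both arms gives 34.7, or 35.65 with the small-sample t-correction, essentially the stated 35.6.

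So 36 per group follows only if the control SD is ignored. That is a separate matter; here it means that power is read at 36 per group with SD 2.21. The unadjusted week-24 comparison has SE = 2.21 × √(2/36) = 0.521 and power Φ(1.44/0.521 − 1.96) = 0.79.

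**Case 1: group-by-time dropped, week 0 an outcome row.** With complete data the group term is the mean of the three visit differences.
- Week-12 effect half: (0 + 0.72 + 1.44)/3 = 0.72, half of 1.44.
- Week-12 effect full: (0 + 1.44 + 1.44)/3 = 0.96, a third below 1.44.

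Its SE is 0.521 × √[(1 + 2ρ)/3]. Power for ρ = 0.3 / 0.5 / 0.7 is:

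| Week-12 effect | ρ 0.3 | ρ 0.5 | ρ 0.7 |
|---|---|---|---|
| half (0.72) | 0.47 | 0.40 | 0.34 |
| full (0.96) | 0.71 | 0.62 | 0.54 |

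**Case 2: group-by-time kept, either follow-up visit allowed to count.** With week 0 as an outcome row, the two interaction coefficients are differences in change from baseline. Under exchangeable correlation their correlation is (1 − ρ)/[2(1 − ρ)] = 0.5 whatever ρ is. The chance under no effect that at least one exceeds 1.96 in absolute value is 9.1%. With baseline SPPB as a covariate instead, the correlation is ρ/(1 + ρ), or 0.33 to 0.41 for ρ 0.5 to 0.7, and the chance is 9.5 to 9.3%.

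**Case 3: QIC chooses between the two models.** Simulated GEE, exchangeable, robust standard errors, 36 per group, SD 2.21.
- No effect, ρ = 0.5: QIC chose the model without interaction in about 84% of runs. Testing the group term there, and the week-24 interaction otherwise, rejected in 10.1% and 11.8% of two batches of 800 runs, about 11%. Letting either interaction count when both are kept raised this to about 15%.
- Part of the excess is not selection: the single tests, taken alone, rejected in about 5 to 7% of runs.
- True effect 1.44 with a half-size week-12 effect: QIC dropped the interaction in 24%, 17% and 3% of runs for ρ = 0.3, 0.5 and 0.7; a second simulation gave about 4 to 27%. The group term in the model without interaction averaged about 0.7.

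**The case against.** The strongest reply is that section 10.2 does plan time interactions, so the diluted average is not the intended analysis, and that QIC is described as a gauge of fit, perhaps meant only for the working correlation. The three named covariates are all known at baseline. A joint interaction test at 5% would also be compatible with the text and would not carry the two-visit inflation.

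Much of this stands. A reader might infer that the plan hands the choice of primary test to QIC. It does not say so; the test merely follows from the chosen model because no coefficient is named. A reader might also infer that SPPB will be transformed. The sentence concerns continuous variables in general and never mentions SPPB, so that is possible but not stated. Nor does the text say that either visit may be declared the primary success.

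What does not stand is the claim that the text already settles the matter. The preference for the smallest QIC follows directly after the sentences on covariates and interactions, speaks of the model, and is not restricted to the correlation structure. Nothing says that group-by-time stays whatever the QIC, or that its week-24 term is primary. If only the working correlation was meant, or if a joint test was intended, one sentence would establish it.

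**Conclusion.** The point holds as an under-specified primary analysis that should be corrected. No section fixes the visit or coefficient for SPPB, and the model-choice rule is broad enough to affect it.

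The sizes are conditional. The reduction from 1.44 to between 0.72 and 0.96 requires that QIC is used on the mean model, that it drops group-by-time, that week 0 is an outcome row, and that the group term is reported. In simulation with a half-size week-12 effect, the interaction was dropped in only about 3 to 27% of runs, so a 33 to 50% dilution must not be read as the expected result. The 9% figure requires that either follow-up visit may count. The 11 to 15% figure comes from simulation at ρ = 0.5 and includes some small-sample error of the robust standard errors. The visit correlation and the week-12 effect are assumptions throughout. The documents do not support a conclusion that the trial's result will be diluted or its error rate inflated; they support the conclusion that the plan does not prevent either.

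**What to change.** Replace the model-choice text in section 10.2 with wording such as:

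> The single primary test is the between-group difference in SPPB at week 24, two-sided 0.05, from a GEE with weeks 12 and 24 as outcomes; group, categorical visit and group-by-visit; and baseline SPPB, age, gender and baseline muscle mass index as fixed covariates, with a pre-stated working correlation and robust standard errors, on the untransformed 0 to 12 scale. Week 12 is secondary. QIC is not used to choose the mean model; it may be used only for the working correlation in sensitivity analysis.

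The handling of week-0 SPPB has to be stated, because naming week 24 alone would still leave several tests open. At 36 per group with SD 2.21 and ρ from 0.3 to 0.7, power is 0.79 for the unadjusted week-24 difference, 0.65 to 0.95 for change from baseline, and 0.83 to 0.97 adjusted for baseline SPPB.

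The analysis of variance sentence in the same section should be limited to baseline comparisons or labelled secondary for outcomes, since it can be read as a further test of SPPB.

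The cost is wording only, with no extra participants or visits. The sponsor gives up data-driven choice of the mean model. Participants with neither follow-up visit do not enter this model, so a sensitivity analysis for them should be named alongside it.
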